### Moderator

A professional moderator (JL) with previous experience in communication and group facilitation will moderate all step 1 and step 2 meetings and will also facilitate the step 3 plenary sessions. In the step 3 meeting, two additional moderators will facilitate small-group deliberation among decision makers from each site. All moderators attended our pilot meetings and participated in a preparation session to develop an animation grid, agree on solutions to potential pitfalls, and develop prompts to guide discussions. The moderators will be responsible for welcoming participants, establishing ground rules with them, ensure fair participation, and facilitate deliberation and agreement on the proposed indicators and actions. A member of the research team (AB) will attend all meetings, present the project and the proposed indicators, and answer technical questions.

### Control

In control sites, quality-indicators prioritisation will be done by clinicians and managers only, following the format described for the above step 2 and step 3 meetings. Public representatives will not be involved in quality-indicator prioritisation.

For research purposes, we will also conduct step 1 meetings in all control sites to collect data on local public recommendations (see the Data Collection and Analysis sections below). The format and content of the step 1 meeting will be identical in control and intervention sites. The moderator and participants will be blinded to their allocation until the end of the meeting. We will present the results of this public consultation to control sites' decision makers at the very end of the step 3 meeting, after we collect all trial outcome data on quality-indicator choice and intended use.

The six participating sites are more than 100 km apart from one another, clinicians and managers have rare contact among themselves, and they serve rather captive populations who receive most of their care within their community, thus minimising the potential for contamination across intervention and control groups. We will ask all participants to respect the confidentiality of discussions and not to share any information in between meetings. We will assess for potential contamination among participants in all meetings.

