### Recruitment and randomisation of the participating sites

The local health authorities' Chief Executive Officers (CEOs) and GMF medical directors from all six territories of Abitibi-Témiscamingue agreed to participate in the study (response rate = 100%). Site randomisation will be done after the recruitment process of individual participants is completed, using a random allocation software [77]. Randomisation will be carried out by one of the researchers, with two independent observers present, and will be concealed to the professionals in charge of recruitment, the group facilitator, and participants until the end of the step 1 meeting (see Control section below).

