### Step 3: decision makers' meeting

In the step 3 meeting, decision makers identified by the local health authority's CEO will choose which indicators to use as local targets for improvement and identify actions to implement these indicators in clinical practice and management. While step 1 and step 2 meetings will be held locally within each participating site, we will hold one semiregional step 3 meeting that will bring together decision makers from all intervention sites, and another semiregional meeting with all control sites. A semiregional format will allow us to involve senior directors from the Regional Health Authority and send consistent messages across all sites regarding the Regional Health Authority's expectations.

Local and regional recommendations developed in steps 1 and 2 meetings will be presented to decision makers. Individual recommendations will be communicated to decision makers by reporting the rank of each indicator, calculated from the proportion of participants who recommended each indicator. Group recommendations and individual recommendations will be color-coded to facilitate their identification by decision makers. Recommendations will be discussed in small-group deliberation sessions within each site. At the end of the meeting, each local health authority's CEO will summarise the decisions and actions proposed within his/her own territory. A Regional Health Authority representative (RL) will be present to explain the quality indicator expected use, describe the professional and technical resources that will be available to support quality-indicator implementation, and answer questions.

Public involvement in the step 3 meeting will combine consultation and deliberation methods. Decision makers will receive written feedback about individual recommendations made by public representatives in step 1 meetings (consultative component). Public representatives who participated in step 1 and step 2 meetings will also be invited to attend the meeting (target: two participants/site) to answer decision makers' questions and assist them in their choice (participation component).

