### Sample size

Our sample size calculation is based on pragmatic considerations and takes into consideration the maximum number of available sites/clusters in the region (n = 6 sites) and the maximum number of recommended participants in small-group deliberation meetings (n = 15 participants per meeting). We aim to recruit a total of n = 90 public representatives, n = 72 clinicians and managers for the step 2 meeting, and n = 60 senior managers and professional council representatives for the step 3 meeting. We will allow for overlap between clinicians and managers participating in step 2 and step 3 meetings.

Abelson and colleagues note that small sample sizes are hard to overcome in studies of public participation in healthcare as 'deliberation decision-making dictates small groups' [13]. We expect that the power of our study will be further decreased by the cluster nature of the trial, although we are currently unable to estimate the magnitude of this effect due to the absence of prior trials of public involvement in quality-indicator prioritisation and unknown intra-cluster coefficients for our outcome of interest [93].

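### Blinding at Step 1 is worded to end with 'the meeting', but one moderator runs all six in turn and the presenting researcher is not listed as blinded, so later public reference lists may be collected unblinded

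*Protocol article*

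**What the plan says.** Under Recruitment and randomisation of the participating sites, the order of events is: "Site randomisation will be done after the recruitment process of individual participants is completed". Allocation then "will be concealed to the professionals in charge of recruitment, the group facilitator, and participants until the end of the step 1 meeting". The Control section repeats the rule for the moderator and participants: "The moderator and participants will be blinded to their allocation until the end of the meeting". It also says that Step 1 has the same format and content in both arms.

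Three other statements determine how this works in practice:

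- The section on the Step 3 meeting says that "step 1 and step 2 meetings will be held locally within each participating site".
- The Control section says: "The six participating sites are more than 100 km apart from one another".
- The Moderator section says that one professional moderator "will moderate all step 1 and step 2 meetings and will also facilitate the step 3 plenary sessions", and that a member of the research team "will attend all meetings, present the project and the proposed indicators, and answer technical questions". The section on quality-indicator prioritisation adds that this member reads out each item at Steps 1 and 2.

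Public representatives record their five priorities at the end of Step 1. Under Statistical analysis, the primary outcome is the correlation between professional and public priorities, and each site's selected indicators are compared with the top five of its own local public list.

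**The concern.** The rule is worded for one meeting, but the person it is meant to blind attends six. Sites more than 100 km apart with one shared moderator cannot hold one-day meetings together, so the meetings follow one another. If allocation is disclosed when each site's meeting closes, the moderator carries that knowledge to the next site. Under a fixed split, each disclosure narrows what remains.

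The presenting researcher is a separate gap that does not depend on the timetable. Neither list of blinded roles includes this person, who explains the indicators to the public.

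What is at stake is the reference list. In intervention sites it will be fed to decision makers; in control sites it is collected for research only. A moderator or presenter who knows which applies could train or explain differently, without intending to, and so shift the list or its reliability by arm. Each site's list is small: 15 people with five choices give 15 × 5 = 75 votes over 37 items, an average of 75 / 37 ≈ 2 per item. A few votes could change which indicators are in the top five.

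**Working it through.** **Is site-by-site disclosure the right reading?** Step 1 is described as a one-day meeting with a target of 15 public representatives per site, held locally. The Step 1 section uses the end of the meeting for the moment when that site's representatives record their priorities. On the same usage, blinding ends at the close of each site's own meeting. The singular could also mean the close of Step 1 as a whole. The article gives no timetable that would settle it.

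**Is a 3:3 split supported?** No ratio is stated. The Step 2 target for clinicians and managers is 72. Suppose k intervention sites have nine each, and the 6 − k control sites fill the maximum of 15:

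9k + 15(6 − k) = 72, so 90 − 6k = 72, so k = 3.

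Neighbouring values fail (k = 2 gives 78, k = 4 gives 66). But 12 × 6 is also 72, so the figure supports 3:3 without proving it.

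**What can the moderator deduce?** Assume 3:3, meetings in sequence, and each allocation known after that site's meeting. There are 20 equally likely orders.

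| Meeting | Already certain | Odds when not certain | Best guess correct |
|---|---|---|---|
| 1 | 0 | even | 0.5 |
| 2 | 0 | 3:2 | 0.6 |
| 3 | 0 | 3:1 (40% of orders), even (60%) | 0.4 × 0.75 + 0.6 × 0.5 = 0.6 |
| 4 | 10% | 2:1 (90%) | 0.1 + 0.9 × 2/3 = 0.7 |
| 5 | 40% | even (60%) | 0.4 + 0.6 × 0.5 = 0.7 |
| 6 | 100% | – | 1.0 |

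- Sites known with certainty, on average: 0.1 + 0.4 + 1 = 1.5 of 6.
- By order: exactly one site known in 12 of 20, two in 6, three in 2. Check: (12 × 1 + 6 × 2 + 2 × 3) / 20 = 1.5.
- Best guesses correct, on average: 0.5 + 0.6 + 0.6 + 0.7 + 0.7 + 1.0 = 4.1 of 6, against 3.0 with no disclosure.
- Of the 4.5 sites not certain on average, 1 + 0.6 + 0.6 = 2.2 are coin-flips, 1 is at 3:2, and 0.4 + 0.9 = 1.3 are at 3:1 or 2:1.

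**Sensitivity to the split.** Under a fixed 2:4 split (15 orders) the average known with certainty is 1.73. Under independent simple randomisation of each site, nothing can be deduced from earlier disclosures.

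**After the change.** With no disclosure until all six meetings are finished, no site is certain, and under 3:3 the expected number of correct guesses is 3.0.

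**The case against.** The strongest reply is that the key facts are inferred. The wording may mean the end of the Step 1 phase, the ratio is not given, and a condensed article may leave the release schedule to the full protocol. That stands as a limit on the size of the problem. It does not dispose of the point, because the article states an end to blinding, and its natural reading is the one that lets blinding wear away.

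The second reply is that the design already protects Step 1. The format is identical in both arms, moderators agreed a common guide and prompts, items come from a fixed written menu, and each person answers alone. Participants attend only their own site's meeting, so their blinding is intact and any bias must act through the moderator or presenter. No direction for it is evident, since professionals' priorities are first measured at Step 2. Agreement is also calculated at baseline, where an arm difference in the public list might show. All of this is right and makes a large bias less likely; none of it keeps the two people running the meeting blind.

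Three stronger readings are tempting and should not be made:

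- A reader might infer that the presenting researcher knows all six allocations. The article says only that one of the researchers randomises, with two independent observers, and does not say which. Not being listed as blinded is a gap, not a statement that the person is unblinded.
- A reader might infer that any resulting bias would be undetectable. The Process evaluation section plans two independent observers and video recording at every meeting, with evaluation questionnaires on facilitation and information received. Differences in conduct could be examined, although an uninfluenced list could not be recovered.
- A reader might infer that every site not known with certainty is strongly predictable. The table shows that about half of them are coin-flips.

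**Conclusion.** The point holds as a weakness in the stated disclosure rule. On its natural reading, the moderator's blinding erodes across the six Step 1 meetings. Under site-by-site release and a fixed 3:3 split, at least one meeting is always run with the allocation known, 1.5 of 6 are on average, and three are in 10% of orders. Under simple randomisation, or if the rule means the end of the whole phase, this part falls away. The omission of the presenting researcher from the blinded roles rests on none of those assumptions.

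The effect on the primary outcome cannot be sized from the document. It is a risk to the reference list, limited by the planned safeguards and not shown to favour either arm. Since removing it costs little, the change should be made.

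**What to change.** State that allocation is withheld from the moderator and from the research team member who presents the indicators until the last Step 1 priority questionnaire from all six sites has been collected, with another team member holding the list. Sites and participants should be told after that same point, so that the moderator does not learn a result in the room. Alternatively, draw the allocation at that point; this still follows completed recruitment. Either version works whatever the allocation ratio.

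Disclosure should not also wait for the professionals' baseline questionnaires. These are completed at the start of Step 2, which public representatives attend only in intervention sites, so allocation must be known by then.

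The cost is in timing: Step 2 invitations to public representatives can go out only after the last Step 1 meeting. No data are lost and no extra staff are needed, provided an existing team member outside the meetings can hold the list.

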### Data collection

Table 4 describes the questionnaires that will be used for data collection. Specific data collection instruments are described in detail below. Research questionnaires were pretested with 21 persons, before being used in our three pilot meetings (described above).

**Table 4 T4:** List of questionnaires

#	Timing	Respondents	Data collected
Q1	Beginning of step 1	Public	Public representatives' sociodemographic data (age, gender, ethnic group, language, education, socioeconomic status, health status, health services use, prior attitude toward public involvement)

Q2	End of step 1	Public	Quality-indicators prioritisation (public baseline priorities)

Q3	End of step 1	Public	Participants' evaluation of the step 1 meeting

Q4	Step 2 and step 3 meetings	Clinicians and managers	Clinicians and managers' sociodemographic data (age, gender, ethnic group, language, education, socioeconomic status, professional role, prior attitude toward public involvement)

Q5	Beginning of step 2	Clinicians and managers	Quality-indicator prioritisation (clinicians and managers' baseline priorities)

Q6	End of step 2	Clinicians, managers, and public representatives	Quality-indicator prioritisation (postdeliberation priorities)

Q7	End of step 2	Clinicians, managers, and public representatives	Participants' evaluation of the step 2 meeting

Q8	End of step 3	Clinicians, managers, and public representatives	Quality-indicator prioritisation, attitude and intention to use the selected indicators for quality improvement (decision makers' choice and intention to use)

Q9	End of step 3	Clinicians and managers (control sites only)	Quality-indicator prioritisation (postconsultation priorities); this questionnaire is completed after we collect data on decision makers' choice and intention to use, and after we present results of public consultation to control sites

Q10	End of step 3	Clinicians, managers, and public representatives	Participants' evaluation of the step 3 meeting

### Quality-indicator prioritisation

Our primary outcome is the comparison of indicator choice and agreement with public priorities between intervention and control groups. Data on quality-indicator prioritisation will be collected at baseline and at the end of each meeting (Figure 3). In order to collect public baseline priorities from all participating sites, we will hold step 1 meetings with public representatives from the six participating sites. Clinicians and managers' baseline priorities will be collected at the beginning of the step 2 meeting. Postdeliberation priorities will be collected at the end of the step 2 meeting. Decision makers' choice and final priorities will be collected at the end of the step 3 meeting. We will also collect postconsultation priorities from control site participants at the end of the step 3 meeting, after we collect data on decision makers' choice and intention to use and present results of public consultation. Postdeliberation and postconsultation priorities will be used for process evaluation purposes to assess the contribution of each component of the intervention.

**Figure 3 F3:**
[figure not shown]
**Data collection on quality-indicator prioritisation**. Participants' priorities will be collected from each site at baseline and after each meeting.

The questionnaire on quality-indicator prioritisation includes the menu item title, a description of the indicator under each item (*e.g.*, 'percent of family physicians who accept new patients'), as well as the source of information (patients' charts, administrative data, or survey) and original reference (Additional File 1). At the end of each questionnaire, participants are asked to prioritise five quality indicators ('indicate the five indicators that you believe are the most important to improve chronic disease prevention and management in your territory') and to rank these five indicators in order of importance [80].

In step 1 and step 2 meetings, a research team member (AB) will read each item individually and answer questions. Participants in these two meetings will be asked to rate each indicator according to its perceived importance and feasibility, using a Likert scale from 1 to 9 [2]. In step 3, participants will be sent the indicator by mail before the meeting. Decision makers will be asked to prioritise their five most important indicators after they receive feedback on individual and group recommendations.

### Decision makers' intention to use the selected indicators

The questionnaire on decision makers' attitude and intention toward indicator use will be completed by all participants in the step 3 decision makers' meeting, after decision makers agree on which indicators they will select as targets for improvement for their territory. We have developed this questionnaire from known predictors and instruments used to measure the likely adoption of quality indicators and health innovations [75,81-85]. The questionnaire consists of 11 items covering decision makers' attitude toward selected quality indicators (importance, feasibility, credibility, group consensus) and their intention to use and report on the selected indicators for quality-improvement purposes. Each item is scored on a 7-point Likert scale.

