### Description of the intervention

The intervention is composed of three one-day meetings (step 1, step 2, and step 3) that aim at prioritizing local quality indicators. The Regional Health Authority expects that the selected indicators will be used to support continuous quality improvement of chronic disease prevention and management (rather than for external control or benchmarking), and each local health authority will be allowed to select its own indicators. The selected indicators will be integrated in the regional accountability contracts signed with each local health authority. Table 3 summarises the topics addressed in each intervention meeting, and their content is described in detail below.

**Table 3 T3:** Intervention meetings' content

Meetings	Participants	Content
**Step 1: Public representatives' training and recommendations**	Public representatives (Target: 15/site)	• Participants' discussion on positive and negative experience in relation to quality of care • Information on chronic disease and local prevention and management services • Explanation of the indicator menu and data collection on baseline public recommendations

**Step 2: Group recommendation**	Clinicians and managers (Target: 9/site) and public representatives (Target: 6/site)	• Individual baseline prioritisation • Deliberation on indicator choice ○ Block 1 (Structure: access and integration) ○ Block 2 (Process: technical quality and interpersonal care) ○ Block 3 (Outcome indicators) • Final group recommendation and individual recommendations

**Step 3: Decision makers' meeting**	Clinicians and managers (Target: 10/site) and public representatives (Target: 2/site)	• Expectations from the Regional Health Authority on quality-indicator choice and use • Presentation of recommendations issued in step 1 and step 2 meetings • Deliberation on indicator choice and implementation • CEOs summarise decisions and foresee actions for each local health authority

CEO = chief executive officer.

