### Statistical analysis

Descriptive statistics will be used to summarise the characteristics of the study population and assess the comparability of intervention and control groups, as well as to summarise data on quality-indicator choice, intended use, and on the marginal costs of the intervention.

We will descriptively report which quality indicators are selected as targets for improvement within each site at the end of the trial and calculate the proportion that are in agreement with local public baseline priorities (ranks 1 to 5). Individual quality-indicator priorities will be analysed as a dichotomous measure by reporting the proportion of participants who selected each indicator as part of their five priorities and by calculating its rank (rank 1 = indicator selected by the greatest proportion of participants). Agreement with public priorities will be analysed by calculating the correlation between professionals (clinicians and managers) and public priorities at baseline and at the end of the trial (primary outcome). Cluster randomisation leads to a reduction of effective sample size and can give spurious statistical results if it is not accounted for properly [93,94]. We will check the data to assess the level of clusterisation within study sites and use appropriate cluster-level analysis (*e.g.*, multilevel modelling) if necessary. We will also compare decision makers' intention to use the selected indicators and participants' satisfaction between intervention and control sites. Statistical significance will be assumed at *p *< 0.05 (two-tailed test) for all tests.

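### Satisfaction at steps 2 and 3 is compared between arms without limiting respondent type, although public representatives respond only in intervention sites; the respondents for intention and the timing of questionnaire Q10 also need settling

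*Protocol article*

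**What the plan says.** The planned comparison is one sentence in the Statistical analysis section: "We will also compare decision makers' intention to use the selected indicators and participants' satisfaction between intervention and control sites". In the same paragraph the agreement outcome is limited to professionals, defined there as clinicians and managers. Satisfaction carries no such limit.

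Table 4 (Data collection) lists three respondent groups for questionnaires Q7 (evaluation of step 2), Q8 (choice and intention, end of step 3) and Q10 ("Participants' evaluation of the step 3 meeting"): clinicians, managers and public representatives. The section on intention says that its questionnaire "will be completed by all participants in the step 3 decision makers' meeting". Table 4 describes the Q8 content as "attitude and intention to use the selected indicators for quality improvement (decision makers' choice and intention to use", although public representatives are among its respondents.

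The Control section says: "In control sites, quality-indicators prioritisation will be done by clinicians and managers only". It also says that, for research purposes, "we will also conduct step 1 meetings in all control sites to collect data on local public recommendations". Control-site decision makers are shown those public results "at the very end of the step 3 meeting, after we collect all trial outcome data on quality-indicator choice and intended use".

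**The concern.** Whether a public representative answers Q7 or Q10 is decided by the allocation itself, since such respondents are absent from steps 2 and 3 in control sites. Randomisation therefore does not balance respondent type in this comparison. If lay members and professionals use the satisfaction scale differently, an arm difference appears even when the intervention does nothing to professionals' ratings.

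The same problem would reach intention, which is specific aim 1b, if the Table 4 label were taken to define the analysis group.

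Separately, the protection against early disclosure in control sites names choice and intended use but not satisfaction. The evaluation form covers the information received and overall satisfaction. A control participant who completes Q10 after seeing the public results is rating a meeting that has by then included part of the intervention's consultative component.

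**Working it through.** **Head counts reproduced.** From Table 3 and the Sample size section:
- Step 1: 15 × 6 = 90, which matches the stated 90.
- Step 3: 10 × 6 = 60, which matches the stated 60.
- Step 2: 9 × 6 = 54 does not give the stated 72. Three intervention sites with 9 professionals and three control sites with 15 do: 3 × 9 + 3 × 15 = 72. The 3:3 split and the 15 per control site are assumptions that fit the total.

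**Public share of respondents.** Table 3 gives the step 3 targets per site as "Clinicians and managers (Target: 10/site) and public representatives (Target: 2/site"; for step 2 they are 9 and 6.
- Step 2 (Q7), intervention: 6/(9 + 6) = 0.40; control: 0.
- Step 3 (Q8, Q10), intervention: 2/(10 + 2) = 0.167; control: 0.

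**Shift in the arm difference with no effect on professionals.** Shift = public share × (public mean − professional mean). The documents do not give the gap, so a range is shown on the 7-point scale.

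| Assumed gap | Step 2 | Step 3 |
|---|---|---|
| 0.5 | 0.40 × 0.5 = 0.20 | 0.167 × 0.5 = 0.08 |
| 1 | 0.40 | 0.17 |
| 2 | 0.80 | 0.33 |

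The step 2 column applies to satisfaction only. The step 3 column applies to Q10, and to Q8 only if all its respondents were pooled.

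**Effect on a nominal two-sided 5% test, 1-point gap.** Assumed: SD 1.0 to 1.5, a normal two-sample test, clustering ignored. With w the public share and g the gap, the intervention-arm variance is SD² + w(1 − w)g². The standard error is the square root of (that variance/n for intervention + SD²/n for control).
- Step 2, 45 vs 45, SD 1.0: variance 1 + 0.24 = 1.24; SE = √(1.24/45 + 1/45) = 0.223; 0.40/0.223 = 1.79; rejection rate 43%. With SD 1.5 it is 23%.
- Step 3, 36 vs 30, SD 1.0: variance 1 + 0.139 = 1.139; SE = √(1.139/36 + 1/30) = 0.255; 0.167/0.255 = 0.65; rejection rate 10%. With SD 1.5 it is 7%.

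**With clinicians and managers only.** Step 2 becomes 27 vs 45 and step 3 becomes 30 vs 30. The shift from lay versus professional mix is then zero by construction.

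**Timing of Q10.** Table 4 places Q8, Q9 and Q10 all at the end of step 3. Only Q9 is stated to follow the presentation of public results, and only choice and intention data are stated to precede it. The Process evaluation section has the evaluation form handed out at the end of each meeting, and the Control section puts the presentation at the very end of step 3. These statements allow Q10 to fall on either side.

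**The case against.** A reader might infer that intention is compared over everyone who attends step 3. The documents do not support that. The passage on all participants says who fills in the form, not who is analysed. The comparison is worded as decision makers' intention. Table 2 defines the step 3 decision-maker category as clinicians and managers, and the step 3 section describes public representatives as assisting them. What remains for intention is that Table 4 attaches the decision-maker label to answers from all three groups.

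A reader might also infer that public representatives are wholly absent from control sites. They attend step 1 there in the same format, so step 1 satisfaction (Q3) is like for like. End-of-trial agreement is already limited to professionals.

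On timing, it is tempting to say that control participants do rate step 3 after the disclosure. That rests on the row order of Table 4, which is weak evidence. The documents permit it but do not state it, and nothing in them shows which way it would move the ratings.

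Finally, satisfaction comes from a process-evaluation form and is not an outcome under aim 1, and the choice of respondent subset is often left to a fuller plan. This limits the weight of the point but does not remove it. The article itself states the satisfaction comparison without restriction, while restricting agreement in the same paragraph. Questionnaire order is also a matter of conduct, which no analysis can repair once the forms are collected.

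**Conclusion.** The point holds for satisfaction at steps 2 and 3: followed as written, the plan sets a mixed group against a professional-only group. The 40% and 17% shares rest on the document's own targets. The size of any distortion depends on a public-professional gap that the documents do not give, and the rejection rates depend further on the assumed SD, the 3:3 split and independence of respondents. They illustrate the direction and order of the problem, which is larger at step 2, and are not forecasts.

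For intention, the passages are inconsistent and need reconciling; no pooled comparison is stated. For Q10, the order is open and exposure before rating is possible. The consequences are confined to a secondary aim and a process measure.

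**What to change.** 1. State in the Statistical analysis section that between-arm comparisons of Q7, Q8 (intention) and Q10 use clinicians and managers only in both arms, with public representatives' answers reported separately and descriptively.
2. Align the Table 4 entry for Q8 and the section on intention with that statement, so that the decision-maker label does not cover public representatives' answers.
3. In control sites, collect Q10 together with Q8, before the public results are presented, and add satisfaction to the data that the Control section protects.

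The cost is a few words and moving one form earlier in the control step 3 meeting. No new data are needed provided the forms show respondent type, which should be at hand because the two groups already give background data on separate questionnaires. The restricted comparison leaves out the intervention-arm public respondents (18 at step 2 and 6 at step 3 under a 3:3 split), who have no counterpart in control.
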